**Methods/design:**

The present study is a randomized, double-blind, placebo-controlled, parallel groups clinical trial approved by the Ethics Committee of our Institution. Thirty-six volunteers (body mass index (BMI) > 35 kg/m^2^) between 18 and 45 years of age will be randomized to the WBS group (WBSG) or control (Sham) group (ShamG) after being submitted to BS. Preoperative assessments will include maximal and submaximal exercise testing, body composition, blood inflammatory markers, and quadriceps strength and endurance. The second day after discharge, body composition will be evaluated and a 6-min walk test (6MWT) will be performed. The WBS or Sham protocol will consist of 30 daily sessions for 6 consecutive weeks. Afterwards, the same assessments that were performed in the preoperative period will be repeated.

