### Evaluations (testing procedures or measurements)

All enrolled volunteers will be submitted to anamnesis and the Baecke questionnaire will be administered to collect information about habitual physical activity related to occupation, sports, and leisure activities [18].

After the screening period and signing the informed consent (Additional file 2), the volunteers will return to the laboratory on 4 different days to perform the preoperative evaluations (Fig. 2), which are: 1) maximal CPX; 2) the 6MWT; 3) blood collection; 4) bioimpedance measurements; and 5) isokinetic and isometric peripheral muscle strength and endurance assessments. All evaluations will be performed again following the intervention.

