**Fig. 2 Fig2:**
[figure not shown]
Consolidated Standards of Reporting Trials (CONSORT) flow diagram of the study. 6MWT 6-min walking test, CPX symptom-limited or maximum cardiopulmonary exercise testing

The CPX will be performed on a treadmill (Super ATL, Porto Alegre, Rio Grande do Sul, Brazil) using the incremental Bruce protocol. Volunteers will be monitored by a 12-lead electrocardiogram (WinCardio System, Microme, Brasilia, Brazil) supervised by a physician, and encouraged to achieve maximal effort. Heart rate, blood pressure, and subjective responses of dyspnea and fatigue by the CR10 scale [19] will also be measured.

The 6MWT will be performed according to guidelines established by the ATS/American College of Chest Physicians [20]. The object of this test is to walk as far as possible for 6 min over a 30-m corridor. Cardiorespiratory and metabolic variables will be collected breath-by-breath through a portable Oxycon Mobile® ergospirometer (Mijnhardt/Jäger, Würzburg, Germany) throughout the 6MWT.

Blood samples will be collected the morning after a 12-h fast from the upper limb antecubital vein by a qualified professional to quantify fasting glucose levels, insulin, the insulin resistance index by the Homeostasis Model Assessment method (HOMA-IR), and the lipid profile (total cholesterol, high-density lipoprotein cholesterol (HDL-C), low-density lipoprotein cholesterol (LDL-C), very low-density lipoprotein cholesterol (VLDL-C), and triglycerides) [2, 21]. It will also be used to measure the serums concentrations of TNF-α, adiponectin, leptin, and myostatin. These samples will be analyzed by enzyme-linked immunosorbent assay (ELISA) in duplicates using high-sensitivity kits (Quantikine® HS, R&D Systems, Minneapolis, USA) according to the manufacturer’s recommendations [22]. The volunteers will be instructed not to exercise for 48 h preceding the examination and to maintain their usual diet.

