### Postoperative data collection

In the PO period, the 6MWT and body composition measurements will be performed. These evaluations will occur within 1 week after discharge. Afterwards, volunteers will be randomized to the experimental group or the control group. At the end of the interventional trial, all preoperative evaluations will be performed a second time.

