### Postintervention data collection

All preoperative assessments will be performed at the end of the intervention period. At the end of the protocol and assessments, all volunteers will receive a report with all data evaluations.

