### Statistical analysis

A blinded researcher will perform all statistical analyses for this study. The volunteers will be codified by the researcher responsible for randomization to ensure blinding of control and intervention groups. Descriptive statistics including the mean, standard deviation (SD), and quartiles will be applied to summarize the data. The Shapiro Wilk test will be used to investigate data distribution. Data will be expressed as mean, SD, and 95% confidence interval. The primary analysis is to assess the effect of the intervention on 6MWT distance and the secondary analysis is the relationship between 6MWT distance and the lean mass loss.

In this sense, the effect of WBS will be assessed in the context of the following hypotheses:H0: WBS does not improve 6MWT distance and/or does not prevent the loss of muscle mass.H1: WBS increases 6MWT distance and/or prevents the loss of muscle mass.

If the data present a normal distribution, analysis of variance (ANOVA) will be tested for comparisons between the body composition and 6MWT distance change considering three periods of evaluation (preoperative, postoperative, and postintervention). In instances where data are not normally distributed, nonparametric tests will be applied.

The benefits obtained by both groups will be demonstrated through the difference between postintervention results minus PO data with all variables that will be collected. Comparisons between groups will be assessed using the unpaired Student *t* test or Mann-Whitney test, as appropriate.

Effect size will be analyzed using Cohen’s *d*, and the results will be interpreted based on the Cohen classification [34] as follows: small (0.21–0.49), medium (0.50–0.79), or large (> 0.80).

The statistical analysis using correlation will assess the degree of association (or dependence) between improvements in functional tests, body composition data (InBody 720 and DXA), muscular assessment (dynamometry), and concentration of cytokines.

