## Abbreviations

6MWT: Six-minute walking test
BMI: Body mass index
BS: Bariatric surgery
COPD: Chronic obstructive pulmonary disease
CPX: Cardiopulmonary exercise test
CVD: Cardiovascular disease
DXA: Dual energy x-ray technique using digital absorptiometry
ELISA: Enzyme-linked immunosorbent assay
HDL-C: High-density lipoprotein cholesterol
LDL-C: Low-density lipoprotein cholesterol
PO: Postoperative
RYGB: Roux-en-Y gastric bypass technique
ShamG: Control group
TNF: Tumor necrosis factor
VLDL-C: Very low-density lipoprotein cholesterol
WBS: Whole-body neuromuscular electrical stimulation
WBSG: Whole-body neuromuscular electrical stimulation group
WHO: World Health Organization

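### Benefit is defined as postintervention minus postoperative for all variables, but CPX, blood markers and dynamometry have no postoperative value

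*Protocol article*

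**What the plan says.** The Statistical analysis section of the protocol article sets one change score. The benefit in both groups is to be shown through "the difference between postintervention results minus PO data with all variables that will be collected". The next sentence gives the group comparison as an unpaired t test or a Mann-Whitney test. The Abbreviations list fixes the term: "PO: Postoperative".

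The content of that visit is described twice, in agreement. Postoperative data collection says: "In the PO period, the 6MWT and body composition measurements will be performed". The Methods/design part of the abstract says: "The second day after discharge, body composition will be evaluated and a 6-min walk test (6MWT) will be performed".

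The preoperative battery, under Evaluations, is longer: "1) maximal CPX; 2) the 6MWT; 3) blood collection; 4) bioimpedance measurements; and 5) isokinetic and isometric peripheral muscle strength and endurance assessments". It is repeated after training: "All preoperative assessments will be performed at the end of the intervention period".

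The same Statistical analysis section plans correlations for the "association (or dependence) between improvements in functional tests, body composition data (InBody 720 and DXA), muscular assessment (dynamometry), and concentration of cytokines".

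**The concern.** A rule that applies to every variable needs a postoperative value for every variable. The visit schedule supplies one for only part of the battery. Muscle strength and endurance, insulin resistance and circulating markers are named in the study objective, and exercise capacity in the hypotheses. For these outcomes (exercise capacity in so far as it rests on the CPX) the analyst would have to find a substitute for the stated change score.

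The substitute matters in two places. First, a change from the preoperative visit spans the operation, whereas a change from the postoperative visit starts after it. Calling the former a benefit obtained within a group would mix surgery with training. Second, the correlations of improvements could end up pairing a 6MWT or body composition change over one interval with a cytokine or torque change over a longer one. If the choice is left until the data are in, the baseline could be picked after results are seen.

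**Working it through.** The documents give no figure on this point to reproduce. The check compares the assessments made at each visit.

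| Assessment block | Preoperative | Postoperative | Postintervention |
|---|---|---|---|
| Maximal CPX | yes | no | yes |
| 6MWT | yes | yes | yes |
| Blood collection | yes | no | yes |
| Body composition | yes | yes | yes |
| Isokinetic and isometric strength and endurance | yes | no | yes |

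Sources: Evaluations for the first column, Postoperative data collection and the abstract for the second, Postintervention data collection for the third.

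**Step 1, count.** Five blocks minus the two measured postoperatively leaves 3 of 5 without the value that the rule subtracts.

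**Step 2, what the blood block holds.** The text after Figure 2 says the sample is taken "to quantify fasting glucose levels, insulin, the insulin resistance index by the Homeostasis Model Assessment method (HOMA-IR), and the lipid profile". TNF-α, adiponectin, leptin and myostatin come from the same collection. So every metabolic and cytokine endpoint falls in a block without a postoperative value.

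**Step 3, can another reading rescue the rule?**
- PO as preoperative: excluded by the Abbreviations list. The ANOVA sentence also names preoperative and postoperative as separate periods.
- All variables as all variables measured postoperatively: the rule then works, but CPX, blood and dynamometry have no stated change score. The three-period ANOVA does not cover them, being confined to body composition and 6MWT distance.
- Gas exchange recorded during the 6MWT may exist postoperatively, but it is not CPX, blood or dynamometry.

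**Step 4, what a preoperative baseline does.** For any variable,

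post − pre = (PO − pre) + (post − PO).

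Randomization follows the postoperative assessment (Recruitment, randomization, and blinding; Postoperative data collection). The term (PO − pre) therefore has the same expected value in both arms.
- Between groups, that term cancels in expectation. The contrast still estimates the effect of the intervention.
- Within a group, it does not cancel. The mean change contains the perioperative shift.
- In a correlation, using (post − PO) for one variable and (post − pre) for the other puts the perioperative shift into only one of the two.

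**The case against.** The strongest case on the other side is that this is one loosely worded sentence. The primary analysis is 6MWT distance, the named secondary analysis is its relation to lean mass loss, and the formal hypotheses concern only 6MWT and muscle mass. All of these are measured postoperatively. The sentence on group comparisons is not expressly limited to postoperative differences, so a t test on postintervention values, or on the change from the preoperative visit, could be run with the data collected. An unadjusted test of that kind would be valid. The visit schedule in Figure 1 is also not shown.

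Most of this stands, and it limits the point. It does not remove the contradiction: the stated rule covers all variables, both text descriptions of the visit exclude three blocks, and the workable alternatives are not the ones the plan names. Nor is this detail that an article leaves to a separate analysis plan, since the article states a rule that its own schedule cannot support.

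Three stronger readings are tempting and are not supported:
- *That the trial would credit bypass surgery to WBS.* Both arms have surgery and are randomized afterwards, so the common effect cancels between groups (step 4).
- *That postoperative-based changes are free of diet and weight loss.* The Discussion describes a liquid diet through the first week and severe dietary restriction especially in the first 3 months. The 6 weeks of training fall within those 3 months. A postoperative baseline leaves out the operation and the immediate recovery, not the continuing restriction.
- *That most of the objective cannot be analysed at all.* It cannot be analysed under the stated rule. The preoperative and postintervention data for it exist.

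**Conclusion.** The point holds as a contradiction within the protocol article. The rule can be carried out for 2 of 5 assessment blocks and not for the other 3: CPX, blood markers, and isokinetic and isometric testing. It also fails for the correlations of improvements that involve dynamometry or cytokines. The count is of assessment blocks, not of ranked outcomes. The primary outcome and lean mass are not touched, and no bias in the randomized comparison follows. What is exposed is a within-group reading of a preoperative-to-postintervention change as benefit, and the mixing of intervals in those correlations.

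This rests on two assumptions: that the two text descriptions of the postoperative visit are complete, and that body composition at that visit includes lean mass.

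**What to change.** Replace the change-score sentence with a short paragraph.

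1. Limit postintervention minus postoperative to 6MWT and body composition.
2. For CPX, blood markers and dynamometry, compare postintervention values between groups by ANCOVA, adjusting for the preoperative value and for sex, the stratification factor.
3. Say that the within-group change in those variables includes the effect of the operation, and do not call it a benefit of the intervention.
4. Keep the postoperative baseline for the 6MWT–lean mass association. Moving it to the preoperative visit would add the perioperative change to the named secondary analysis for no gain.
5. Only for correlations involving dynamometry or cytokines, use the preoperative-to-postintervention change for both variables, so that the intervals match, and state that this interval includes surgery.

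The cost is one paragraph of analysis wording, with no new visit, assay or patient. It should be settled before the data are analysed.

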### Volunteers

#### Recruitment, randomization, and blinding

Volunteers will be recruited from among patients included in a waiting list for BS and followed by a multidisciplinary team (composed of a physician, surgeon, anesthesiologist, cardiologist, physical therapist, nutritionist, and psychologist) for a minimum period of 1 year. During this period, volunteers will be counseled on smoking and alcohol cessation and informed about the surgical procedure and PO care.

Eligible volunteers will be evaluated within 1 month before BS, 2 days after discharge and, afterwards, will be randomized to the experimental or control group with a 1:1 allocation ratio by a computer-based permuted block randomization (www.randomization.com). To achieve a gender balance for both protocols, the randomization will be stratified by gender and two randomization plans for each gender will be proposed with blocks of 4. The randomization sequence will be generated by an independent research assistant and the intervention protocol will be applied by a physical therapist. Since the present study is a double-blind clinical trial, the volunteers, the physical therapist who will perform the assessments, and the researcher who will perform the statistical analysis will be blinded to the allocation of the volunteers.

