#### Sample size

The sample size calculation was performed using GPower, Version 3.1.3 (Franz Faul Universität Kiel, Germany), based on a previous study by our group performed on BS patients [16] which showed a difference between the distance walked during a 6-min walking test (6MWT) before and after aerobic training of 49.7 ± 15 m. We hypothesize that we will see an improvement in 6MWT distance following WBS to a similar level as our previous study. Therefore, we projected a sample size that would provide 80% power at a significance level of α = 0.05, detecting a variation of 30% as a favorable outcome. These parameters indicate a sample of five volunteers would be required to investigate functional gains after the intervention.

The primary outcome measure for the study will be the 6MWT distance in meters since the distance walked following interventions in patients with chronic conditions is an important tool to assess the efficacy of interventions that theoretically improve functional capacity [16]. Secondary outcomes of this study are to investigate whether the intervention prevents muscle mass loss and whether there is an association between 6MWT distance with lean mass in kilograms [17]. Therefore, since the performance improvement, the prevention of lean mass loss, and the association between these measures represent important outcomes in the present study, the sample size was recalculated. Based on the bivariate normal correlation model, considering a significance level of 5%, a sample power of 95%, and a strong correlation (> 0.70) between lean mass percentage and 6MWT performance as the main outcome, the calculated sample size was 16 volunteers per group. Anticipating a dropout rate of approximately 15%, a total of 36 patients will be included in the present study.

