Appropriate correlation tests will be used if normality of distribution, linearity, variability, and homoscedasticity is satisfied from the scatter diagram performed a priori. The correlations will be defined as weak (0.20–0.50), strong (0.50–0.70), and very strong (> 0.70) [35]. The statistical analysis will be performed using SPSS Statistics for Windows, Version 17.0. (SPSS Inc., Chicago, IL, USA) and MedCalc, version 11.4.4.0 (MedCalc Software, Mariakerke, Belgium), adopting a significance level of 5%. Per-protocol and intention-to-treat analyses will be conducted.

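### Two unranked analyses are given for the primary 6MWT outcome, and neither adjusts for pre-treatment distance or the gender stratum; name one baseline-adjusted primary model

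*Protocol article*

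**What the plan says.** All references are to the protocol article.

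- **Sample size** fixes the endpoint: "The primary outcome measure for the study will be the 6MWT distance in meters".
- **Statistical analysis** makes the intervention effect on that distance the primary analysis and then describes two analyses that include it.
  - The first: "analysis of variance (ANOVA) will be tested for comparisons between the body composition and 6MWT distance change considering three periods of evaluation", the periods being preoperative, postoperative and postintervention. Its fallback is general: "In instances where data are not normally distributed, nonparametric tests will be applied".
  - The second takes postintervention minus PO for every variable collected: "Comparisons between groups will be assessed using the unpaired Student" t test or Mann-Whitney, whichever is judged suitable. A Shapiro-Wilk test is the named check of distribution.
- The same section plans both per-protocol and intention-to-treat analyses and makes neither primary.
- **Recruitment, randomization, and blinding** says that "the randomization will be stratified by gender". Gender appears in no planned analysis.
- **Evaluations** and **Postoperative data collection** show that 6MWT is measured twice before randomisation: before surgery and within a week of discharge.

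**The concern.** The article should let a reader identify the one comparison that decides the primary question. Here the ANOVA and the change-score test can disagree, and nothing says which prevails. Within each, the form of the test depends on a normality test in about 16 patients per arm, where such a test is a weak guide.

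The two pre-randomisation distances and the stratum are also not used as covariates. Subtracting the PO value removes only part of the baseline variation unless the visits are highly correlated. The ANOVA treats two visits that precede treatment as outcome periods. In a trial of 36, any precision already in the data is worth keeping, and an unadjusted comparison leaves a chance imbalance in starting distance or gender uncorrected in this sample.

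**Working it through.** **1. The plan's own figures.** The 16 per group rests on a correlation of 0.70 with 95% power at 5%, not on a comparison of 6MWT between arms. The Fisher z formula, n = ((z_α + z_β)/atanh(ρ))² + 3, gives one-sided ((1.645 + 1.645)/0.867)² + 3 = 17.4, so 18. Simulated one-sided power at 16 is 94.5%, so 16 is approximately reproduced (two-sided power is 89.9%). For dropout, 32/0.85 = 37.6, so 38 against the stated 36; 36 × 0.85 = 30.6 completers. The choice of primary 6MWT test enters none of these figures.

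**2. Reference point.** In the first 6MWT calculation ("we projected a sample size that would provide 80% power"), 30% is not tied to a base. If it means 30% of 49.7 m, the effect is 14.91 m; with SD 15 m this is 14.91/15 = 0.99 SD, and a two-sided t test with 16 per arm has 77.7% power. The comparison below fixes the change-score t test at 80%, an effect of 1.023 SDs of change. If the true difference from sham were the full 49.7 m with SD 15 m, every method would have power near 100%, and adjustment would affect only the width of the interval.

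**3. Formulas.** Assume equal SDs at all visits and between-visit correlation ρ. The article does not give ρ, so a range is shown.
- ANCOVA on PO against change score: variance ratio (1 − ρ²)/(2(1 − ρ)) = (1 + ρ)/2.
- ANCOVA on PO and preoperative value, all visits equally correlated: (1 − 2ρ²/(1 + ρ))/(2(1 − ρ)).

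**4. Results.** 16 per arm, two-sided 5%, 40,000 simulated trials per row. The last model includes a gender term with no gender effect assumed.

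| ρ (assumed) | Variance ratio, PO only | Power, PO only | Variance ratio, PO + preoperative | Power, PO + preoperative + gender |
|---|---|---|---|---|
| 0.5 | 0.75 | 88.8% | 0.667 | 90.9% |
| 0.7 | 0.85 | 84.7% | 0.706 | 89.2% |
| 0.8 | 0.90 | 82.3% | 0.722 | 88.5% |
| 0.9 | 0.95 | 80.9% | 0.737 | 88.1% |
| 0.95 | 0.975 | 79.6% | 0.744 | 87.6% |

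The change-score test had 79.6% to 80.2% in the same runs. Type I error was about 5% for all three methods.

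**5. Sensitivity to the correlation pattern.** The last two columns assume that the preoperative walk predicts the final walk as well as the PO walk does. If correlation decays with time (AR(1)), the preoperative value adds nothing once PO is in the model and costs a degree of freedom. At ρ = 0.8, power is 82.3% with PO alone and 80.9% with both; at ρ = 0.93 it is 78.5% with both.

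**6. Cost of leaving the analyses unranked.** Under the null, with equal correlations and ρ from 0.5 to 0.9, each test alone holds about 5%. Claiming success if either the change-score t test or the group-by-period ANOVA is significant gives 7.3% to 8.0%. This is an upper bound, reached only if the better result is picked.

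**The case against.** **The change-score test is valid.** This stands. Under randomisation it is unbiased with the correct type I error. A reader might infer that the plan gives a distorted result; the article does not support that.

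**The pre-treatment values are used.** This also stands. PO is subtracted in the change score, and the preoperative value enters the ANOVA. A reader might infer that both are ignored; the accurate statement is that neither is a covariate and that the t test makes no use of the preoperative value. Nor may one say that the t test is the primary test, since the article gives it no such label.

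**The gain may be negligible.** This largely stands. If the 15 m in Sample size is the SD of change (the article does not say), then 15² = 2·SD²·(1 − ρ). Assumed between-patient SDs of 30, 40 and 60 m give ρ of about 0.88, 0.93 and 0.97, where ANCOVA on PO gains nothing useful. The planned ANOVA, read as a group-by-period test, has about 84% under equal correlations, slightly above ANCOVA on PO at ρ = 0.8. So the claim that ANCOVA always gives more power fails. No gain from gender has been shown, because no gender effect was simulated.

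**The normality switch is rule-driven.** Partly right: it follows a named check, so it is not four free choices. Two unranked analyses remain.

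**An article condenses.** Covariates and model form may sit in a fuller document, and their mere absence would be no finding. But the article states its methods for the primary outcome, and the point concerns those stated methods.

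**Conclusion.** The point holds as a weakness in pre-specification and efficiency. Two analyses of the primary outcome stand unranked, and neither adjusts for the PO distance, the preoperative distance or the gender stratum. It is not a bias, and no figure in the article changes.

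The pre-specification part needs no assumption. The efficiency part depends on ρ, with equal SDs assumed: at 16 per arm and 80% change-score power, ANCOVA on PO gains about 8 points at 0.5, 5 at 0.7, 2 at 0.8, and nothing at 0.9 or above. Adding the preoperative value gives 88% to 91% only if all visits are equally correlated; if correlation decays it brings little or nothing beyond PO alone. At very high ρ the adjusted model can lose up to about 2 points. The case for adjusting is therefore a gain at moderate correlation against a small possible loss, together with an analysis that reflects the stratified design.

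**What to change.** In Statistical analysis, name one primary analysis of 6MWT: a linear model (ANCOVA) of postintervention distance on group, PO distance and gender, in all randomised patients, reported as an adjusted difference with 95% CI.

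- State the sidedness. The article sets 5% without it, and its alternative is directional ("WBS increases 6MWT distance and/or prevents the loss of muscle mass").
- The preoperative distance may be added, if prespecified.
- Do not choose the primary test by Shapiro-Wilk. Use a rank-based or permutation version as a sensitivity analysis.
- Label the three-period ANOVA and the change-score t test as supportive.

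The cost is a change of wording, made while recruitment is under way, with no new data or visits. The model uses two degrees of freedom for covariates, three with the preoperative value; the power this can cost is given in the verdict.

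### The association between 6MWT change and lean-mass change, which set the sample size, is planned as a correlation with no term for randomised group; adjusting for group is better whether the arms are pooled or analysed separately

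*Protocol article*

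**What the plan says.** Under Statistical analysis, the primary analysis is the effect on 6MWT distance, and "the secondary analysis is the relationship between 6MWT distance and the lean mass loss". The method comes later in the same section: "The statistical analysis using correlation will assess the degree of association (or dependence) between improvements in functional tests", body composition, dynamometry and cytokines. Benefit is measured for each patient as the "difference between postintervention results minus PO data with all variables that will be collected", so the variables being correlated are change scores. On the choice of test, the section adds only: "Appropriate correlation tests will be used if normality of distribution, linearity, variability, and homoscedasticity is satisfied". No group term, partial correlation or regression is named, and pooling of the arms is neither stated nor excluded.

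Under Sample size, the number of patients was recalculated for this association, using a bivariate normal correlation above 0.70, a 5% significance level and 95% power, and "the calculated sample size was 16 volunteers per group". The alternative hypothesis is that "WBS increases 6MWT distance and/or prevents the loss of muscle mass", so an effect on both variables is one of the outcomes the trial anticipates.

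**The concern.** In a two-arm trial, a plain correlation between two changes can be run in two ways, and each has a drawback.

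- **Over all patients.** If treatment moves both outcomes, the two arms form separate clouds of points, and the line joining their centres adds to the correlation. The result can be the treatment effect seen twice, with no link between gaining distance and keeping lean mass among patients treated alike. If the treatment effects run in opposite directions, a real link can be hidden.
- **Within each arm.** The distortion disappears, but each test uses half the patients. The plan then has two answers and no rule for the case where they disagree.

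At stake is the interpretation of the named secondary result and of the other planned correlations. The primary between-group comparison of 6MWT distance is not affected.

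**Working it through.** **Inputs from the protocol.** 16 patients per arm; 1:1 allocation; target correlation 0.70; 5% level (sidedness not stated); 95% power; correlations of 0.50-0.70 labelled strong; Cohen's d of 0.50-0.79 labelled medium and above 0.80 large.

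**Assumed.** The between-arm effect on each change score is not given. It is taken as d within-arm SDs and varied over a range. Tests are two-sided at 5%.

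**1. The plan's own figure.** By Fisher z, n = ((z_alpha + z_power)/atanh(0.70))^2 + 3, with atanh(0.70) = 0.867.
- One-sided: ((1.645 + 1.645)/0.867)^2 + 3 = 17.4, so 18. The exact bivariate normal calculation gives 17, with 94.5% power at 16.
- Two-sided: ((1.960 + 1.645)/0.867)^2 + 3 = 20.3, so 21. The exact calculation gives 20, with 89.9% power at 16.

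So 16 is close to the one-sided answer for a single correlation. That fits a plan to correlate within each arm.

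**2. Pooled reading.** With no within-arm correlation and effects d1 and d2, the pooled correlation is

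r = (d1 d2/4) / sqrt((1 + d1^2/4)(1 + d2^2/4)).

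For d1 = d2 = 1 this is 0.25/1.25 = 0.20. Rejection rates below come from 40,000 simulated trials of 2 x 16.

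| Shift on both changes (SD) | Induced r | Pooled test rejects |
|---|---|---|
| 0.5 | 0.06 | 6% |
| 0.8 | 0.14 | 12% |
| 1.0 | 0.20 | 20% |
| 1.5 | 0.36 | 57% |
| 2.0 | 0.50 | 91% |

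The group-adjusted partial correlation (29 degrees of freedom) rejects in 4.9% to 5.3% in every case tried. If only one outcome responds, the pooled rate also stays at 5%. In the opposite direction, a within-arm correlation of 0.50 with shifts of +0.8 and -0.8 SD gives a pooled r of 0.29 and 35% power, against 84% adjusted.

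**3. Per-arm reading.**

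| True within-arm r | Power, one arm of 16 | Power, group-adjusted on 32 |
|---|---|---|
| 0.50 | 53% | 84% |
| 0.60 | 73% | 96% |
| 0.70 | 90% | 99.7% |

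The chance that exactly one arm is significant is 2 x 0.53 x 0.47 = 50% at r = 0.50, and 2 x 0.90 x 0.10 = 18% at r = 0.70.

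95% intervals for an observed r of 0.50, by Fisher z:
- One arm: 0.549 ± 1.96/sqrt(13), which gives 0.01 to 0.80.
- Adjusted for group, n - 4 = 28: 0.549 ± 1.96/sqrt(28), which gives 0.18 to 0.73.
- Adjusting for gender as well (n - 5 = 27) changes this only to 0.17 to 0.73.

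**4. Limit of the adjustment.** If the correlation is 0 in sham and 0.70 under WBS, the adjusted correlation averages 0.35 with 51% power, against 90% in the WBS arm alone. A comparison of the two arms' correlations has standard error sqrt(2/13) = 0.392. For 0.70 versus 0, 0.867/0.392 = 2.21, so power is about 60%. For 0.70 versus 0.30, (0.867 - 0.310)/0.392 = 1.42, so power is about 30%.

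**The case against.** The strongest reply is that the article does not specify the analysis being criticised. It neither says that arms are pooled nor excludes a group term, and such detail often sits in a fuller document. The one textual hint, sizing per group, points to per-arm correlations, which have no treatment-induced component. This stands in part: it cannot be said that the trial will report a spurious association. But the article does fix correlation of improvements as the method for the analysis that sized the trial, and both ways of carrying that out are inferior to a standard alternative.

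Several stronger readings are tempting and are not supported:

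- A reader might take 49.7/15 = 3.3 SD from Sample size as the expected effect on 6MWT distance. With an assumed 1 SD on lean mass, that gives a pooled rejection rate of 63%. But 49.7 ± 15 m is a before-after change with aerobic training in an earlier study. Here sham patients do the same exercises without current, so the figure is not a between-arm effect in this trial.
- A reader might infer that the per-arm analysis is underpowered for its own target. At 0.70 it still has 90% two-sided power; the loss matters mainly below that.
- A reader might infer that pooling always misleads. Inflation is slight at 0.5 SD and absent if only one outcome responds, which the and/or in the hypothesis allows. Reaching the strong label (0.50) by this route alone needs about 2 SD on both.
- A reader might infer that adjustment settles everything. It does not if the slopes differ between arms.

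It can also be said that a marginal correlation is a genuine association. That is true, but it does not show whether patients who keep lean mass walk further when treated alike.

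**Conclusion.** The point holds in this limited form. The association is to be tested without a group term and with pooling unspecified, and a group-adjusted estimate is better under either reading. The gain under pooling depends on assumed between-arm effects that the protocol does not give: it runs from negligible (6% against 5%) at 0.5 SD on both changes to large (57%) at 1.5 SD. Under per-arm analysis, which the text favours, the gain is in precision: from 53% to 84% power at a correlation of 0.50, and from 90% to more than 99% at 0.70. Both power figures for the adjusted analysis assume 16 evaluable patients per arm and the same within-arm correlation in both. This is a worthwhile correction to a secondary analysis and does not bear on the primary comparison.

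**What to change.** In Statistical analysis, replace the plain correlation with this: the association between change in 6MWT distance and change in lean mass (postintervention minus postoperative) will be estimated in all randomised patients with both values, as a partial correlation or regression slope adjusted for randomised group and for gender (the stratification factor), with a 95% confidence interval, using a rank-based partial correlation if the assumptions fail. Apply the same adjustment to the other planned correlations.

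Beside it, report the correlation in each arm with its confidence interval and the group-by-lean-mass interaction. A non-significant interaction should not be read as proof of a common slope, since that test is weak at 16 per arm.

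The cost is analysis wording, two degrees of freedom and the common-slope assumption. No extra patients or measurements are needed, and the blinded analyst can make the adjustment with coded group labels.
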